### Feasibility measures

The primary outcome of this study will be the feasibility and acceptability of the delivery of PM+EP in refugee youth. Feasibility will be determined through criteria related to consent and recruitment rates (>70%), attendance to PM+/PM+EP sessions (>70%), protocol adherence by helpers (>75%) and the number of AEs (<10%). In this study, AEs were defined as any unwanted experiences during the study, regardless of relation to PM+or PM+EP. Serious AEs (SAEs) are events causing death, life threat, hospitalisation or its prolongation, permanent disability or other significant medication conditions not necessarily connected to the intervention. All AEs/SAEs will be reported and followed, with specialist referral as needed. Regarding the feasibility of the research procedure, the completion of the baseline and follow-up assessments will be assessed (>85%). In addition, the qualitative process evaluation will further elucidate information of the acceptability of the interventions.

Protocol adherence will be determined through two methods. The first is a self-rated fidelity checklist that the PM+/PM+EP facilitators will fill out at the end of each session. This will contain each of the elements from the completed session, and facilitators will be asked to identify what items they completed and which items they may have missed to assess the degree of fidelity to the manualised intervention. second, audio recordings of sessions will be taken if participants provide informed consent for recording. A random sample of 10% of recordings will be scored independently by two research assistants.

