### Problem management plus

PM+ is a brief, potentially scalable psychological intervention developed by the WHO and is delivered by non-specialised helpers.^17^ In brief, the intervention is based on cognitive behavioural therapy techniques and typically consists of 5 weekly, 90 min sessions. Participants are taught the following techniques during the sessions: stress management, problem-solving, behavioural activation and accessing social support (WHO, 2016). The intervention is described in detail elsewhere.^17^

For this study, a translated and adapted version (to the Swedish context) of PM+ will be used to match the exposure between the two active intervention arms. There will be 6 weekly 75 min sessions as opposed to 5. For the PM+arm, the additional session will include non-directive supportive counselling to match the time spent on the ‘emotional processing’ module.

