### PM+ with EP module (PM+EP)

The PM+ strategies discussed above are identical across both interventions apart from the additional EP module.^28^ The additional module aims to provide a safe environment for participants to engage in the EP of both positive and negative memories. During the additional session, participants will be asked to imagine significant memories as pieces of a jigsaw puzzle; participants will be asked to elicit three memories, two positive/pleasurable and one negative/frightening. Participants will be assisted in processing these memories through discussing the puzzle pieces, the thoughts and emotions that come with the memory, and future perspectives. Participants will be asked to rate the intensity of emotions before and after they talk about their memories each time they are brought up.^28^ By constructing a life story, the participant is provided with the opportunity to adequately contextualise significant events, which may facilitate the recognition of interrelated emotional networks of experiences. Since this module will be added to a transdiagnostic intervention to reduce psychological distress, the distressing event may be a traumatic event, or any other adverse event (AE) with negative impact. Previous research has indicated that interventions involving exposure to traumatic memories can be safely administered to adolescents through the process of task-shifting.^31^ The additional module includes the following specific components:

Psychoeducation: Participants will be informed about the rationale behind the module and the mechanisms associated with it.Choosing three pieces of their ‘jigsaw puzzle’ (memories): Participants will be asked to choose three memories, two of them being pleasurable memories and one difficult (distressing/frightening/upsetting) memory. Participants will be asked to give a label to each of these memories (eg, ‘leaving the country’, ‘meeting with best friend’).EP of memories: After the ‘puzzle’ is ready, participants will be asked to talk about the memories on their lifelines. Participants will be asked to first discuss the positive memory and then the difficult memory. Talking about the same difficult memory will last for three sessions. Each time it is discussed, a discussion about a positive memory will follow.Positive imagination for the future: The final part of this module aims to help participants to engage in positive thinking by asking them to imagine their future in a positive way.

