The additional EP components will occur between sessions 3 and 6.

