### Analysis plan

The primary analyses for the feasibility RCT are planned to understand the safety and acceptability of the intervention and to preliminarily understand the within-group changes prior to and following the PM+(EP) Interventions. To accomplish this, both quantitative and qualitative methods will be used. The data will be analysed for the primary outcome and the other continuous measures using repeated measures analysis of variance. Kruskal-Wallis tests will be used if the normal distribution assumption fails. For the feasibility evaluation, intervention-specific analysis (fidelity, attendance to sessions) will be carried out. The qualitative process evaluation data will be analysed following thematic analysis through NVivo Scientific Software. To estimate potential effectiveness for a future trial, intention-to-treat analyses will be employed. Cohen’s d, based on pooled SD, will be used to calculate the treatment effect size of the PM+EP (based on primary outcome).

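### The delivery criteria contain no reading of the EP module, so if attendance is counted over scheduled sessions they can be met while up to 8 (or 11) of 20 PM+EP youth receive no EP

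*Protocol article*

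**What the plan says.** The Feasibility measures section states: "The primary outcome of this study will be the feasibility and acceptability of the delivery of PM+EP in refugee youth". Its delivery criteria are "attendance to PM+/PM+EP sessions (>70%), protocol adherence by helpers (>75" per cent. The other criteria there cover consent and recruitment, adverse events and completion of assessments. None concerns receipt or delivery of EP.

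On content, the section on PM+ with EP module says: "The PM+ strategies discussed above are identical across both interventions apart from the additional EP module". On timing, the same section says "The additional EP components will occur between sessions 3 and 6" and, of the exposure work, "Talking about the same difficult memory will last for three sessions". On course length, the Problem management plus section says "There will be 6 weekly 75 min sessions as opposed to 5". For the PM+ arm it adds that "the additional session will include non-directive supportive counselling to match the time spent on the ‘emotional processing’ module", which treats EP as worth one session.

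Adherence comes mainly from a checklist that the helper completes after each session, marking which of that session's elements were done or missed. A 10% sample of recordings is scored independently. The Analysis plan adds that "intervention-specific analysis (fidelity, attendance to sessions) will be carried out". The Sample size section gives 20 youth per arm.

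**The concern.** PM+EP differs from PM+ only by EP, so showing that PM+EP can be delivered means showing that EP can be delivered. The Introduction poses this question itself: can ingredients of exposure therapy be delivered through a scalable intervention? The failures to look for are youth leaving when memory work begins and lay helpers leaving it out.

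The stated thresholds cover the course as a whole. The early sessions and the shared PM+ content count alongside EP, so a pass on both need not say anything about EP. The conclusion on the primary outcome, and the planning of a definitive trial, could then rest on figures that mainly describe ordinary PM+.

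**Working it through.** The 70% and 75% thresholds are chosen, not derived, so there is no plan figure to reproduce. The check is a count of what the thresholds allow.

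**Inputs.** 20 youth in the PM+EP arm (Sample size); 6 sessions each (Problem management plus); so 20 × 6 = 120 scheduled sessions. Attendance must exceed 70%, that is, more than 84 of 120. EP starts at session 3 or after session 3, depending on how the timing sentence is read.

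**Attendance as percentage of scheduled sessions.** If k youth each miss the last m sessions and everyone else attends all six, attendance is (120 − m·k)/120.

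- EP in sessions 3 to 6, leaving after session 2 (m = 4): k = 8 gives 88/120 = 73.3%, a pass; k = 9 gives 84/120 = 70.0%, a fail. Up to 8 of 20 (40%) receive no EP.
- EP in sessions 4 to 6, leaving after session 3 (m = 3): k = 11 gives 87/120 = 72.5%, a pass; k = 12 gives 84/120 = 70.0%, a fail. Up to 11 of 20 (55%) receive no EP.
- EP as a single session (m = 1): all 20 can miss it, at 100/120 = 83.3%.

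**Less favourable attendance among those who stay.** If stayers attend 90% of their sessions (5.4 of 6), the total is k(6 − m) + 5.4(20 − k).

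- m = 4: k = 7 gives 14 + 70.2 = 84.2, or 70.2%, a pass; k = 8 fails. The limit is 7.
- m = 3: k = 9 gives 27 + 59.4 = 86.4, or 72.0%, a pass; k = 10 gives exactly 70.0%, a fail. The limit is 9.

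**Other definitions of attendance.**

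- Each participant must attend over 70% of sessions: 4/6 = 66.7% is too few and 5/6 = 83.3% is enough. A participant who meets this misses at most one session, so cannot miss all EP if EP spans three or four sessions.
- Over 70% of participants must complete the course: 14/20 = 70.0% is too few, so 15 are needed and at most 5 of 20 (25%) can miss EP.

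**Adherence.** The checklist covers sessions that took place, so a youth who has left contributes nothing that lowers the score. If EP makes up a share s of the checklist items and only EP is omitted, adherence is 1 − s, which exceeds 75% whenever s < 25%. The article does not give s, so it must be assumed:

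| EP share of items (assumed) | Adherence with no EP delivered | Share of the arm in which EP can be skipped with a pass |
|---|---|---|
| 1/6 | 83.3% | all |
| 25% | 75.0% (fails) | just under all |
| 30% | 70.0% (fails) | just under 83% |
| 40% | 60.0% (fails) | just under 62.5% |
| 50% | 50.0% (fails) | just under 50% |

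The last column is 0.25/s, with all other items delivered.

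**With an EP reading added.** In the two main attendance examples, 12/20 = 60% and 9/20 = 45% receive any EP. Both would fail a threshold of more than 70% applied to EP receipt.

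**The case against.** The strongest reply is that the article nowhere says the criteria average over sessions. It gives two percentages without denominators, and a condensed article may leave the definition to the full protocol. Under a completer definition both attendance examples fail (60% and 45%). This stands, and it makes the attendance point conditional.

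The examples are also worst cases, and they do not all rest on one picture of EP. The 40% and 55% limits need EP spread over several sessions, on different readings of the timing sentence. A youth who leaves after session 3 has already had one EP session if EP begins in session 3. The 83.3% adherence figure needs EP to be about one-sixth of the items. The module lists psychoeducation, memory selection, repeated processing and future imagination, so its share could be larger.

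A reader might infer that the trial would hide a failure of EP. The documents do not support that. Checklists are kept by item and session, recordings are sampled, estimating drop-out is a stated purpose of the sample, and the interviews cover helpers and, where feasible, dropouts. The problem would be visible in planned data; it is only that no criterion uses those data. Nor does the article make the two percentages an automatic trigger for a definitive trial.

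A reader might also infer that PM+ attendance can carry PM+EP through one joint figure. The promised intervention-specific analysis points the other way, and the Introduction sets the aim for both interventions, so naming both in one criterion is not itself an error. Separating the arms does not, however, remove the mixing of EP with non-EP sessions: every attendance example above uses the PM+EP arm alone.

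Finally, whole-package attendance and fidelity are legitimate feasibility measures. That is true; the case is for adding to them, not replacing them.

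**Conclusion.** The concern holds in a bounded form. The stated criteria for delivering PM+EP include nothing specific to EP. On the plain percentage-of-sessions reading, the PM+EP arm can pass with up to 8 of 20 youth (EP in sessions 3 to 6) or 11 of 20 (EP in sessions 4 to 6) receiving none, falling to 7 and 9 if the others attend 90% of sessions. Under per-participant or completer definitions the attendance gap largely closes. On adherence, complete omission of EP passes only if EP is under 25% of checklist items, which the article does not let one determine; at larger shares partial omission can still pass.

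These figures are limits on what the rules permit, not forecasts. They justify an inexpensive improvement to the criteria. They do not show that the trial would miss a failure of EP.

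**What to change.** In the Feasibility measures section:

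1. Apply the attendance and adherence criteria to the PM+EP arm separately from PM+.
2. State the attendance denominator: scheduled sessions, participants reaching a set number of sessions, or participants completing the course.
3. Add two EP readings to the conclusion that PM+EP is feasible: (a) the proportion of youth randomised to PM+EP who attended the sessions in which the difficult memory is processed, reported for any and for all such sessions, against the existing 70%; (b) the proportion of EP checklist items completed in PM+EP sessions, against the existing 75%. State in advance whether the any or the all figure decides (a).
4. Reconcile the Problem management plus section with the section on PM+ with EP module. EP is described both as one additional session and as spread over several, and (a) has no defined denominator until this is settled.

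The cost is wording and some extra tabulation of session records and checklists already planned. Recruitment began in October 2024, so the change should be dated and made before attendance and fidelity are examined by arm. The downside is a stricter criterion resting on 20 youth: 15 of 20 are needed to exceed 70%, and each youth moves the figure by 1/20 = 5 percentage points.

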### Trial design

The study consists of two phases: a feasibility RCT and a qualitative process evaluation. The feasibility RCT uses a three-armed single-blind randomised controlled parallel group design, comparing PM+, PM+EP and care as usual (CAU) for forcibly displaced persons living in Sweden. We aim to recruit 60 participants who screen positive for moderate psychological distress. Assessments will be conducted at baseline, 1 week after treatment completion (7 weeks) and 3 months after treatment completion (19 weeks). The flow chart of the trial is shown in figure 1. As part of the qualitative process evaluation, we will be exploring beneficiaries’ and implementers’ experiences with the intervention, and practitioners’ and policymakers’ thoughts on the use of PM+/PM+EP more widely in Sweden.

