### Study procedure

Potential participants will be recruited through ongoing Save the Children Sweden activities in three regions of Sweden (East, South and West). Save the Children Sweden has available programmes for children, young people and caregivers nationally. In 2024, activities reached almost 40 000 children and young people. These programmes included psychosocial activities, group-based mental health support and safe meeting places where displaced persons were able to receive support. Recruiting staff at Save the Children will inform all young people about who may meet the eligibility criteria about the possibility of participating during their regular activities. If recruitment for the final sample size is not possible through ongoing Save the Children services, advertisements will be placed on social media with information about the study. Potential participants who indicate interest in participation are then referred to the study team and perform an initial screening assessment of eligibility using the WHODAS 2.0, K10 and a structured suicide risk evaluation assessment. Participants will be invited to the baseline assessment if they meet the eligibility criteria stated above and consent to participating in the trial. At baseline, participants will complete the following assessments: HSCL-25, PCL-5, PSYCHLOPS, WHO-5, bonding social capital, SHS-A and CSRI. In addition, participants will be asked to complete PMLD and the traumatic event checklists. Following the assessment, participants will be randomly assigned in a consecutive manner, using a 1:1:1 ratio for the randomisation process. The randomisation sequence will be computed by an independent researcher from KI using computerised software and allocation will be conducted by Save the Children Sweden; allocation is concealed from all study staff. Following the completion of the intervention, participants will be invited to complete 1-week postintervention (7-week) and 3-month follow-up (18-week) assessments.

After the 3-month follow-up, participants will be invited to take part in the qualitative process evaluation. Individual semistructured qualitative interviews will be conducted by researchers and psychologists. Interviews with participants and their families will be held in their preferred language. For key informants, interviews will be conducted on an ongoing basis throughout the trial, and for PM+EP/PM+helpers, at the conclusion of their final sessions.

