### Sample size

Since this is a pilot feasibility trial, no formal power calculations have been carried out. A total number of 60 forcibly displaced youth (20 in each arm) will be included in the study, allowing us to evaluate the feasibility and acceptability of the intervention in the proposed setting, as well as drop-out rates for a future definitive trial. This sample size was determined to be sufficient based on prior similar studies.^44 45^

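### The <10% adverse-event criterion counts events of any cause and names no denominator or arm, so background events alone can decide the safety verdict on PM+EP

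*Protocol article*

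**What the plan says.** The protocol article makes the feasibility and acceptability of PM+EP the primary outcome and says that feasibility is determined by a list of thresholds (Feasibility measures).

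- **AE threshold.** The list includes "protocol adherence by helpers (>75%) and the number of AEs (<10" (a percentage). The section then states that "AEs were defined as any unwanted experiences during the study, regardless of relation to PM+or PM+EP". It does not say whether the percentage refers to participants, events or sessions, or to which arm or arms it applies.
- **Completion threshold.** For the research procedure, "the completion of the baseline and follow-up assessments will be assessed (>85" (a percentage). The text does not say whether time points are pooled or judged one by one, or who is in the denominator.
- **Order of events (Study procedure).** "Participants will be invited to the baseline assessment if they meet the eligibility criteria stated above and consent to participating in the trial". Then: "Following the assessment, participants will be randomly assigned in a consecutive manner, using a 1:1:1 ratio for the randomisation process".
- **Size and schedule.** "A total number of 60 forcibly displaced youth (20 in each arm) will be included in the study" (Sample size), and "Assessments will be conducted at baseline, 1 week after treatment completion (7 weeks) and 3 months after treatment completion (19 weeks" (Trial design). Study procedure gives 18 weeks for the last visit; the difference does not affect this point.

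Neither threshold is derived, and "no formal power calculations have been carried out".

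**The concern.** Recording AEs regardless of cause is good practice. The difficulty is using that all-cause count as an absolute pass mark for the intervention. Participants are selected for distress and impaired functioning and are followed for about four months, so some will have unwanted experiences unrelated to PM+EP. A fixed limit with no relatedness judgement and no contrast with care as usual (CAU) cannot separate those from harm done by the intervention. A harmless PM+EP could fail.

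The missing denominator adds a second problem: the same data can pass or fail according to the reading chosen at analysis.

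The completion criterion raises a related question. Baseline precedes randomisation, so every randomised participant should have one. If baseline is averaged with the follow-ups, attrition is diluted, although the Sample size section names drop-out as something this trial should estimate for a definitive one.

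**Working it through.** There is no derivation in the plan to reproduce. The allocation is consistent: 3 × 20 = 60.

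**1. What the AE limit allows, read as participants with at least one AE.** The proportion must be strictly below 10%. In PM+EP, 2/20 = 10% fails, so at most 1. In both active arms, 4/40 = 10% fails, so at most 3. In all arms, 6/60 = 10% fails, so at most 5.

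**2. How far the reading matters.** Suppose five PM+EP participants have one AE each and nobody else has any. Per PM+EP participant this is 5/20 = 25% (fail). Per participant over all arms it is 5/60 = 8.3% (pass). Per planned PM+EP session it is 5/(20 × 6) = 4.2% (pass).

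**3. Chance of passing when the intervention causes no AE.** Let r be the background proportion with at least one AE. It is an assumption, because the document gives none. With X binomial(n, r), P(pass) = P(X ≤ limit). For n=20 this is (1−r)^20 + 20r(1−r)^19; at r=0.10 that is 0.1216 + 0.2702 = 0.392.

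| Assumed r | n=20 (≤1) | n=40 (≤3) | n=60 (≤5) |
|---|---|---|---|
| 5% | 0.74 | 0.86 | 0.92 |
| 10% | 0.39 | 0.42 | 0.44 |
| 20% | 0.07 | 0.03 | 0.01 |
| 30% | 0.008 | 0.0006 | 0.0001 |

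**4. The same limit on related events only.** At an assumed 2% related rate, P(pass) is 0.94, 0.99 and 0.999 for n=20, 40 and 60. Adding a 20% background gives 1 − 0.80 × 0.98 = 21.6% with any AE, and P(pass) falls to 0.05, 0.02 and 0.006. The background rate, not the related rate, drives the verdict.

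**5. Why an interval is needed.** With 0 of 20 related events, the upper exact two-sided 95% limit is 1 − 0.025^(1/20) = 16.8%. Even the best possible result in the PM+EP arm does not exclude a true rate above 10%.

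**6. Completion, if pooled over the 60 randomised.** There are 3 × 60 = 180 assessments, and 0.85 × 180 = 153, so 154 are needed. With 60 baselines in hand, 94 of 120 follow-ups suffice (78.3%). Missing 13 at each visit gives 60 + 47 + 47 = 154 (85.6%, pass). Missing 14 gives 152 (84.4%, fail). T2 at 60/60 with T3 at 34/60 (56.7%) also totals 154 and passes.

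**7. Completion on follow-ups alone.** More than 102 of 120 are needed, so 103 (85.8%); at a single visit more than 51 of 60, so 52. At a true follow-up rate of 80%, with the 120 assessments treated as independent, the chance of passing is 0.72 pooled and 0.07 on follow-ups only.

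**8. If the denominator is everyone invited to baseline.** Baseline can then fall below 100%. At 85% baseline the pooled rule needs (3 × 0.85 − 0.85)/2 = 85% follow-up, and the dilution disappears.

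**The case against.** The strongest reply on AEs is that the result follows from the assumed rate. At 5% background the criterion is usually met. That stands. A reader might infer that nearly every participant will have an AE, or that the criterion can be met only by under-reporting. The document gives no AE rate, so neither inference is supported.

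A reader might also infer, from the lack of an AE row in Table 1 and of weekly helper contact under CAU, that AEs are not collected comparably across arms. This is an argument from silence in a condensed article. The text says all AEs and SAEs are reported and followed, and CAU participants also have the T2 and T3 assessments. It is not part of this point.

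On completion, the reply is that the text states neither pooling nor a randomised denominator. Baseline is offered by invitation and done remotely, so its completion among invitees can be a genuine feasibility measure. Judged visit by visit, follow-up still has to exceed 85%. This also stands. A reader might infer that the baseline figure is 100% by design and always inflates the result; that holds only under the pooled, randomised reading. What remains is that the text permits that reading.

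Finally, the article calls these feasibility criteria and states no go/no-go rule, so they should not be described as progression rules. They nevertheless determine the primary outcome, alongside other criteria and a qualitative evaluation. Relatedness judgements do bring subjectivity, and the 10% figure remains underived under any definition.

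**Conclusion.** The AE point holds from what the text itself states: an all-cause definition is tied directly to an absolute limit, with no denominator or arm. Read per participant, and with no intervention-related AE, the criterion fails more often than not once about 10% of participants have a background AE, and nearly always at 20%. At 5% it usually passes. These rates are assumptions, and participants are treated as independent. The conclusion is that background events can decide the verdict, not that they will.

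The completion point is secondary and conditional. Only if time points are pooled over randomised participants does the criterion pass at 78.3% follow-up; read per visit, the baseline component is merely uninformative for those randomised. Both are worth correcting because the correction is cheap.

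**What to change.** 1. State the safety threshold as the proportion of PM+EP participants with at least one AE or SAE judged at least possibly related to the intervention or study procedures, with an exact 95% confidence interval. Say who judges relatedness and by what rule.
2. Tabulate all-cause AEs and SAEs by arm, as participants and as events, without a threshold.
3. Apply >85% to T2 and to T3 separately, with all randomised participants as the denominator. Report baseline completion among those invited as a separate figure.

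**Cost.** Mostly wording. Relatedness has to be judged, and the article does not say whether it is already recorded. The completion figure may look less favourable. Recruitment began in October 2024, so the change must be dated and documented before analysis.
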